### Sample size estimation

It was calculated that 126 patients with T2DM would be required in this trial to demonstrate a significant difference at 80% power and 5% significance. Power calculations were based on the literature and aimed at a difference of 0.5% in HbA_1c_ value in the treated group as compared to the placebo group with a standard deviation of 1.0% [30]. With an expected rate of 50% vitamin D deficient participants, 252 subjects would be required. According to an expected drop out rate of 20%, 300 subjects will be recruited.

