Correlation coefficients will be measured using Pearson or Spearman, depending on the level of measurement. A logistic and/or linear regression model will be used for multivariate analysis to relate an outcome variable to causal variables. The multivariate analysis will be used to rule out the possible role of confounders for vitamin D deficiency as season of measurement, maternal age, ethnicity, diet, physical activity and BMI.

Subgroup analyses will be performed by stratifying vitamin D into three groups: deficient (15–49 nmol/l), insufficient (50–74 nmol/l), and sufficient (75–150 nmol/l). Furthermore, subgroup analyses for vitamin D deficient patients (serum 25 (OH) D 15–35 nmol/l), and poor glycaemic control (HbA_1c_ ≥ 53 mmol/mol) will be performed using the same method as described for the primary analysis. A p-value < 0.05 will be considered as statistical significant.

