This trial has several strengths: the study sample size allows us to perform a subgroup analysis of vitamin D deficient patients. Taken into account that only in vitamin D deficient patients an effect of vitamin D supplementation on glycaemic control will be found, we chose to recruit double the number of participants as calculated with the power estimation, hypothesizing that 50% of the included patients will be vitamin D deficient (serum 25 (OH) D < 50 nmol/l). Secondary, the relatively high dose chosen for intervention and the duration of the trial are strengths of our study. The dose of vitamin D supplementation of 50,000 IU of vitamin D per month (daily equivalent ~1667 IU) is based on the recommendations of the Institute of Medicine and on the study done by van Groningen et al. [31,34]. In this latter study, performed in the Netherlands, it was demonstrated that a cumulative dose of 100,000 IU given in 2 months increases the serum 25 (OH) D meanly with 29 nmol/l. Assuming that the mean serum 25 (OH) D in our study population will be around 50 nmol/l at baseline, the serum 25 (OH) D should be raising to a sufficient status (≥75 nmol/l) in two months. To measure a difference in HbA_1c_ level we hypothesize that the maximal effect will be seen at least at six months, regarding the fact that the red blood cells circulate about 100 days in the blood and HbA_1c_ levels takes around six weeks to change. Furthermore, this is the first study examining the association between vitamin D status and skin autofluorescence value as well as the effect on skin AGEs after vitamin D supplementation. For this secondary outcome the duration of our trial will be a limitation, regarding the stability and long half-life of skin AGEs with could be the cause to find no effect of vitamin D supplementation on skin AGEs.

The results of this trial should provide more insight into the potential causal association between vitamin D status and glycaemic control in patients with T2DM.

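### Two groups, 15–49 and 15–35 nmol/l, are both called vitamin D deficient; only the first is powered, and the plan does not say which tests the hypothesis that only deficient patients benefit

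*Protocol article*

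**What the plan says.** All places are in the Protocol article.

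- **Statistical analysis, three strata.** Baseline vitamin D is split into "deficient (15–49 nmol/l), insufficient (50–74 nmol/l), and sufficient (75–150 nmol/l".
- **Statistical analysis, next sentence.** It adds "subgroup analyses for vitamin D deficient patients (serum 25 (OH) D 15–35 nmol/l), and poor glycaemic control". The poor-control group is HbA1c ≥53 mmol/mol. These two added subgroups are to be analysed by the method of the primary analysis. The only significance threshold given is p<0.05.
- **Sample size estimation.** "It was calculated that 126 patients with T2DM would be required in this trial", for a "significant difference at 80% power and 5% significance"; the calculation "aimed at a difference of 0.5% in HbA_1c_ value in the treated group as compared to the placebo group", "with a standard deviation of 1.0"%. Then: "With an expected rate of 50% vitamin D deficient participants, 252 subjects would be required". An expected 20% dropout brings recruitment to 300.
- **Discussion.** An effect on glycaemic control is expected only in deficient patients. Recruitment was therefore doubled, "hypothesizing that 50% of the included patients will be vitamin D deficient (serum 25 (OH) D < 50 nmol/l".
- **Inclusion/exclusion criteria.** Patients with 25(OH)D below 15 or above 150 nmol/l are excluded.

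**The concern.** The deficient subgroup carries this trial's hypothesis and accounts for half of its size, so it needs one definition. Two adjacent sentences give it two upper limits, 49 and 35 nmol/l, and nothing explains the second. The Background and the Discussion both use 50 nmol/l, so 35 is the odd one out.

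Two results would then exist for deficient patients. If they disagree, either could be presented as the prespecified one, and only one has the power for which the trial was sized.

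There is a second, weaker strand. To say that only deficient patients respond is to say that the treatment effect depends on baseline vitamin D. The approach described compares arms inside subgroups and judges each result at p<0.05. A significant result in one stratum and a non-significant one in another does not show that the two effects differ.

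**Working it through.** **1. Reproduce the plan's figure.** Inputs from Sample size estimation: difference 0.5, SD 1.0, 80% power, 5% significance. Sidedness is not stated; two-sided is used here.

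n per arm = 2 × (1.960 + 0.842)² × 1.0² / 0.5² = 62.8, so 63 per arm and 126 in total. This matches.

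126 / 0.5 = 252. This matches too.

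**2. Identify the powered group.** The Discussion's limit is below 50 nmol/l and eligibility starts at 15 nmol/l. The powered group is therefore the 15–49 stratum.

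**3. Power in that group** (normal approximation, Φ(0.5 × √(n/2) − 1.96), with n per arm):

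- 126 of 252, 63 per arm: 80%.
- Completers: 300 × 0.8 = 240. Half is 120, or 60 per arm: 78%.

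**4. Size of the 15–35 group.** The article gives no share and no SD for 25(OH)D. The Discussion assumes a baseline mean of about 50 nmol/l. The following are my assumptions: a normal distribution truncated to 15–150 nmol/l, with SD between 15 and 25.

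Share = [F(35) − F(15)] / [F(150) − F(15)]. At SD 15 this is (0.159 − 0.010) / 0.990 = 15.0%.

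| Assumed SD | Share in 15–35 | Patients of 240 | Per arm | Power (t-test, difference 0.5, SD 1.0) |
|---|---|---|---|---|
| 15 | 15.0% | 36 | 18 | 31% |
| 20 | 19.4% | 47 | 23 | 38% |
| 25 | 21.1% | 51 | 25 | 41% |

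Without any distribution, by the normal approximation, shares of 10%, 20% and 30% of 240 (24, 48 and 72 patients) give 23%, 41% and 56%. All are well below 80%.

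**5. Power of an interaction test.** Take an effect of 0.5 in deficient patients and 0 in the others, SD 1.0, 240 completers, and a fraction f deficient.

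SE = √[4/(240f) + 4/(240(1 − f))]; power = Φ(0.5/SE − 1.96).

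- f = 0.5: SE = 0.258, 0.5/SE = 1.94, power 49%.
- f = 0.2: SE = 0.323, 0.5/SE = 1.55, power 34%.

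**The case against.** **The powered group is analysed.** A reader might infer that the subgroup behind the sample size is not the one singled out for analysis. The text does not support that. The 15–49 stratum is the first of the three planned, and 15–35 is added to it rather than put in its place. This objection stands.

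**Both groups have fixed limits.** Membership is clear and no new cut-off can be introduced after the data are seen. That also stands, and it narrows the problem to labelling and hierarchy. It does not settle which of the two results answers the main question.

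**No power is claimed for 15–35.** True, so the low power contradicts no stated figure. The percentages depend on an assumed SD and shape, and they show only why the two groups cannot stand in for each other.

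**Interaction tests and multiplicity rules may be in a fuller document.** This is fair: the article is condensed, and nothing in it rules out an interaction test. Their absence is therefore secondary to the conflict in definitions. The article does, however, state a within-subgroup comparison for the two added groups, and that approach by itself cannot answer the hypothesis in the Discussion. The sentence on the three strata names no method.

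**Inflated false-positive rate.** A reader might multiply up the 5% tests as if they were independent. The groups are nested and overlapping, so that calculation does not apply, and no such figure is offered here.

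**Conclusion.** The concern holds as a conflict in definition and hierarchy. One label covers two planned groups, and the plan does not say which of them tests the hypothesis that only deficient patients benefit. Only the 15–49 nmol/l group is powered, at 78–80% if half the patients fall in it. The 15–35 group would have about 31–41% power under an assumed mean of 50 and SD of 15–25 nmol/l, or 23–56% if its share is simply taken as 10–30%. The conflict itself is in the text and needs no assumption; only the size of the narrower group does.

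The point about effect modification is a worthwhile improvement rather than an error of equal weight. The sample size arithmetic for 126 and 252 is not in question.

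**What to change.** In the Statistical analysis section:

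1. Name 15–49 nmol/l (below 50 among eligible patients) as the single key subgroup, and say that it is the one on which the sample size rests.
2. Give 15–35 nmol/l a different name, and mark it and HbA1c ≥53 mmol/mol as exploratory.
3. Add a treatment × baseline 25(OH)D term to the primary model, with 25(OH)D preferably continuous. Report the interaction and the stratum estimates from that model with confidence intervals, in place of separate p-values.

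The cost is analysis wording and a little analysis work; recruitment, visits and treatment are untouched. The Trial status section says recruitment is still under way, so the change could be made before unblinding. There are two downsides. Fewer subgroup p-values can be claimed. The interaction test is also weak, with about 49% power at a 50:50 split for effects of 0.5 and 0, so the plan should state that a non-significant interaction is not evidence that the effect is the same at all vitamin D levels.

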## Results

### Study procedure

The study will be divided into two phases: Phase I and Phase II.

#### Phase I

Patients with T2DM who met the inclusion criteria at their last visit at the general practice will be invited through a brief introduction letter for participation. All patients will be approached by phone in three weeks after receiving the letter whether or not they are interested for participation. If interested, the extensive patient information form will be given and an appointment will be scheduled at the general practice for informed consent and start of the trial.

#### Phase II

The trial has a total of three visits at the patient’s own general practice (Figure 1). The initial visit includes informed consent, assessment of eligibility, questionnaires regarding demographics, sunlight exposure, physical activity, dietary intake (fish and dairy products), diabetes history and medication, co-morbidity and health related quality of life (SF-36). Anthropometric parameters and skin AGE accumulation will be measured. Blood collection will be collect at this stage. The study medication will be given for six months with a prior instruction. The second visit at three months is for safety assessment and observation of consumption. This includes: discussion of any adverse events, any change in medication, control of the ingestion of the study medication, blood collection (including serum calcium, renal function, serum 25 (OH) D and HbA_1c_). The final visit is at the end of six months, when questionnaires and anthropometric measurements are repeated and the last set of blood samples are collected (Table 1). The inclusion of all patients will be spread over one year to prevent large seasonal influences, as well as the results will be adjusted for seasonal influences.

**Figure 1 F1:**
[figure not shown]
Recruitment flow chart.

**Table 1 T1:** Outcome variables and time of measurement (n = 300)

**Variables**	**Months**		
	0	3	6
Informed Consent	x		
Sociodemographics	x		
Medical and family history	x		
Diet, sun exposure, physical activity	x		x
Advanced Glycation End products (AGEs)	x		x
Questionnaire SF-36	x		x
Medication alterations		x	x
Adverse events		x	x
** *Anthropometry* **			
Height, weight, BMI	x	x	x
Blood pressure	x	x	x
Waist/hip circumference	x		x
** *Blood analysis* **			
Serum 25 (OH) D	x	x	x
HbA_1c_	x	x	x
Fasting blood glucose	x	x	x
Fasting blood insulin	x	x	x
C-peptide	x	x	x
Serum creatinine	x	x	x
Lipid profile	x		x
Serum calcium	x		x
Serum phosphate	x		x
Serum albumin	x	x	x
Serum PTH	x		x
Serum TSH	x		x
AST	x		x
ALT	x		x
Alkaline phosphatase	x		x
γ-GT	x		x
Hb, Platelets, Leukocytes	x		x
C-reactive protein	x		x
Urine analysis	x	x	x

All participants will be informed of their anthropometry and blood pressure measurement at the start and during the course of the trial. The blood test results during the course of the trial will only be discussed when these are abnormal and lead to premature termination of the trial. The following criteria are drawn for premature termination of the trial: hypercalcaemia (calcium > 2.65 mmol/l), onset of any granuloma forming disease, serum 25 (OH) D < 15 nmol/l or > 250 nmol/l, impaired renal function (eGFR < 30 ml/min), hypersensitivity for cholecalciferol, onset of urolithiasis, change in hypoglycaemic agents or HbA_1c_ > 69 mmol/mol (8.5%). After completion of the trial, all participants will be informed of their blood results. In case of vitamin D deficiency (serum 25 (OH) D < 50 nmol/l) at the end of the trial, supplementation with cholecalciferol will be started. The patients will be informed by letter in which group they participated after every patient completed the trial.

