### Inclusion/exclusion criteria

Adults (≥18 years) with T2DM, diagnosed according to the World Health Organisation, who are treated with lifestyle advises, metformin, or sulfonylurea-derivatives (SU-derivatives), whether or not in combination, were invited for participation. Serum glycated hemoglobin (HbA_1c_) had to be stable and below or equal to 64 mmol/mol (8.0%) for the last three months without recent changes in hypoglycaemic agents.

The exclusion criteria are: an impaired renal function (estimated creatinine clearance < 30 ml/min measured by the MDRD formula: 186 × (serum creatinine)^ -1.154 × (age)^ -0.203 × 0.742 (if the subject is female) or × 1.212 (if the subject is black)), any granuloma forming disorder, known history of renal stones or hypercalcaemia (serum calcium > 2.65 mmol/l), hypo- or hyperphosphatemia, serum 25 (OH) D < 15 nmol/l or > 150 nmol/l, known intolerance for cholecalciferol, using other antidiabetic treatment as mentioned above, insufficient knowledge of the Dutch language, mental retardation or psychiatric treatment for schizophrenia or bipolar disorder, participation in any other trial, being pregnant or lactating, or no signed informed consent.

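### Blood results may be discussed during the trial only if they are abnormal and also end participation, a condition that 14 of the 18 blood rows in Table 1 cannot meet as written

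*Protocol article*

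**What the plan says.** The relevant text is in the protocol article, in the paragraph below Table 1 (Study procedure, Phase II).

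- **Shared with patients throughout:** "All participants will be informed of their anthropometry and blood pressure measurement at the start and during the course of the trial".
- **Blood tests during the trial:** results "will only be discussed when these are abnormal and lead to premature termination of the trial".
- **Termination criteria based on a laboratory value:** the list opens with "hypercalcaemia (calcium > 2.65 mmol/l), onset of any granuloma forming disease". It continues with 25(OH)D below 15 or above 250 nmol/l, eGFR below 30 ml/min, and HbA1c above 69 mmol/mol. The remaining items are not laboratory values: granuloma-forming disease, hypersensitivity, urolithiasis and a change in hypoglycaemic agents.
- **Release of everything else:** "After completion of the trial, all participants will be informed of their blood results".

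Phase II describes the middle visit as follows: "The second visit at three months is for safety assessment and observation of consumption". The bloods it names for that visit include calcium, renal function, 25(OH)D and HbA1c. The Adverse events section covers reporting of serious events to the ethics committee. Neither section says what happens when a laboratory value is abnormal but meets no termination criterion.

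**The concern.** The sentence sets two conditions, joined by 'and' and governed by 'only'. A result that is abnormal but does not end participation fails the second one. For a test that appears nowhere in the termination list, the second condition cannot be met through its own value. The trial would then hold, for example, a markedly abnormal liver enzyme or haemoglobin result that its own text does not allow to be discussed with the patient until the end.

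What is at stake is participant safety and communication. The effect estimate is not involved. This is also not a complaint about something the article leaves out, because the article states a restrictive rule in plain terms.

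**Working it through.** **Step 1: count the tests.** The blood analysis block of Table 1 has 19 rows. One is urine analysis, which a sentence about blood tests does not cover. That leaves 19 − 1 = 18 blood rows.

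**Step 2: match them to the termination list.**

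| Blood rows in Table 1 | Months measured | Termination criterion |
|---|---|---|
| 25(OH)D, HbA1c, creatinine (as eGFR) | 0, 3, 6 | yes |
| Calcium | 0, 6 in Table 1; the text adds month 3 | yes |
| Glucose, insulin, C-peptide, albumin | 0, 3, 6 | no |
| Lipids, phosphate, PTH, TSH, AST, ALT, alkaline phosphatase, γ-GT, blood count, C-reactive protein | 0, 6 | no |

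Covered: 3 + 1 = 4 of 18 (22%). Not covered: 4 + 10 = 14 of 18 (78%). The disagreement over calcium at month 3 is a separate matter and does not change the count.

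**Step 3: how long a result is held.** If completion means the patient's own six months:

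- Baseline result: 6 − 0 = about 6 months, for any of the 14 rows.
- Month-3 result: 6 − 3 = about 3 months, for 4 of the 14 rows.
- Month-6 result: no delay of note, because it belongs to the final visit.

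One row drops out at baseline in practice. Abnormal phosphate ("hypo- or hyperphosphatemia") is an exclusion criterion, so it surfaces at eligibility. That leaves 14 − 1 = 13 rows at baseline with neither an entry rule nor a termination rule.

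**Step 4: the four covered tests.** The article does not define 'abnormal', but its own entry limits and categories give a benchmark.

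| Test | Entry limit | Termination limit | Range not discussed |
|---|---|---|---|
| HbA1c (mmol/mol) | at most 64 | above 69 | above 64, up to 69 |
| 25(OH)D, high (nmol/l) | at most 150 | above 250 | above 150, up to 250 |
| 25(OH)D, low (nmol/l) | at least 15 | below 15 | 15–49, which the article calls deficient |
| eGFR (ml/min) | at least 30 | below 30 | any decline that stays at 30 or above |

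The rule therefore also holds back some results of tests that do have a criterion.

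**The case against.** Several objections deserve weight.

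1. **The safety visit and the rule match.** The month-3 bloods that Phase II names are exactly the four tests with termination criteria. This stands. A reader might infer that the disclosure rule contradicts the purpose of the three-month visit, but on the named tests it does not.

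2. **Few uncovered tests have an interim value.** Ten of the 14 rows have no month-3 draw. This stands, and it confines the point mainly to baseline results. It also answers the thought that phosphate is inconsistently missing from the termination list. Phosphate is screened at entry and next measured at the final visit, so there is no interim value for a termination criterion to act on.

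3. **Baseline may not count as during the trial.** The paragraph does separate the start from the course of the trial for anthropometry and blood pressure. However, Phase II puts consent, eligibility, blood collection and handing out of medication into the initial visit, so baseline results may return after the patient has started. Nothing else in the paragraph releases them earlier. This remains an assumption. If baseline falls outside the sentence, what is left is glucose, insulin, C-peptide and albumin at month 3, and the sub-threshold values of the covered tests.

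4. **Withholding protects the blind.** This is a good reason for 25(OH)D, PTH and calcium. Release of glucose or HbA1c could also prompt changes in medication. It does not explain holding back liver enzymes, TSH or blood counts.

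5. **The article is condensed.** The full protocol or the patient information form may deal with incidental findings, and the sentence does not say that results are kept from the practice. That is possible, but a fuller document allowing discussion would contradict the sentence as printed, so a reconciliation is needed either way.

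**Conclusion.** The point holds as a minor one. As written, 14 of 18 blood rows cannot meet the condition for discussion before the end, and abnormal but sub-threshold values of the other four are held back as well. The main exposure is baseline results, held for about six months. This rests on two assumptions: that baseline results fall under the sentence, and that completion means the patient's own six months.

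Three stronger readings are tempting and are not supported.

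- **A delay of up to 18 months** (12 months of inclusion plus 6 of follow-up) would require completion to mean the whole study. The same paragraph speaks of termination of the trial under patient-level criteria. For the letters on group assignment it says explicitly that every patient must have completed. The individual reading is therefore the more natural one.
- **Damage to the safety outcome.** The sentence governs what is discussed with participants. Nothing in it stops the investigators from recording, reviewing or analysing an abnormal value, or from entering it as an adverse event.
- **A count of 15 of 19 tests**, which would include urine analysis. The sentence speaks of blood tests.

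Sample size and the primary analysis are unaffected.

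**What to change.** Reconcile three places: the disclosure sentence below Table 1, the blood tests listed in Table 1, and the list of termination criteria. After the change, discussion of an abnormal result should not depend solely on its also ending participation. Which results and which values qualify is a clinical decision for the investigators and is not proposed here. The revised text should say whether baseline results are included and whether completion means the patient's own follow-up. It should also say how potentially unblinding results (25(OH)D, PTH, calcium) are handled so that blinding is kept.

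The cost is a reworded sentence and an instruction to the laboratory. The downside is slightly more contact with patients during follow-up, in both arms. Recruitment was in progress when the article was written, so the change could still be of use to patients.

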**Methods/design:**

In a randomised double-blind placebo-controlled trial conducted in five general practices in the Netherlands three hundred patients with type 2 diabetes mellitus treated with lifestyle advises or metformin or sulphonylurea-derivatives are randomised to receive either placebo or 50,000 IU Vitamin D_3_ at monthly intervals. The primary outcome measure is the change in glycated haemoglobin level between baseline and six months. Secondary outcome measures include blood pressure, anthropometric parameters, lipid profile, insulin resistance, quality of life, advanced glycation end products and safety profiles. Quality of life will be measured by The Short Form (SF-36) Health Survey questionnaire. Advanced glycation end products are measured by an AGE-reader.

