### Statistical analysis

The primary efficacy analysis to explore the intervention effect on glycaemic control will be based on the intention-to-treat (ITT) method, in which all randomised patients for whom outcome data are available, will be recorded. In the ITT analysis the patients will be analysed according to their original group assignment, whether or not they accepted and/or adhered to the intervention. This analysis avoids the possibility of any bias associated with loss, misallocation or non-adherence of participants. If there will be a substantial difference between those allocated to receive an intervention and those who actually received it (and adequately adhere to it), we will perform an additional analysis adjusting for actual treatment received (‘per protocol’ analysis). The results of the ‘per protocol’ analysis will be compared with the ITT analysis and the numbers involved will be precisely described.

All raw data will be entered into SPSS software (version 20.0, SPSS Inc, Chicago, IL). Ten percent of all data will be double-entered to check for duplication and outliers before starting statistical analyses.

Baseline characteristics of the study patients will be summarised separately for each randomised group. Dichotomous and categorical data will be presented as number and percentages of patients within both groups. Continuous variables will be checked for normality and will be presented in terms of means and standard deviation if normally distributed, or when a variable has a skewed distribution as median, 25th and 75th percentiles. Nominal variables including subgroups will be analysed using the Chi-squared test, ordinal variables by the Mann-Witney test or Kruskall-Wallis test and continuous variables by the *t*-test or analysis of variance model (ANOVA).

The primary efficacy endpoint, HbA_1c,_ will be compared between placebo and treatment group using a repeated measures analysis of variance with adjustment for baseline characteristics. For secondary outcomes a paired *t*-test, Wilcoxon’s test or repeated measures analysis of variance will be performed. Delta values will be calculated to compare the differences in means over time between the treatment and placebo group.

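### Exit rules tied to HbA1c make some loss outcome-dependent, so the available-data ITT analysis does not avoid all bias from loss as claimed; the bias is modest and towards no effect

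*Protocol article*

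**What the plan says.** All references are to the protocol article.

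- **Primary outcome** (Abstract, Methods/design): "The primary outcome measure is the change in glycated haemoglobin level between baseline and six months".
- **Entry** (Inclusion/exclusion criteria): HbA1c "had to be stable and below or equal to 64 mmol/mol (8.0%) for the last three months".
- **Exit** (text below Table 1): "The following criteria are drawn for premature termination of the trial: hypercalcaemia" opens a list that also contains "onset of urolithiasis, change in hypoglycaemic agents or HbA_1c_ > 69 mmol/mol (8.5"%). The surrounding sentences concern individual patients' results, so this means the end of one patient's participation, not of the whole study.
- **Timing** (Phase II and Table 1): HbA1c is taken at months 0, 3 and 6. Month 6 is the final visit.
- **Analysis set** (Statistical analysis): an ITT analysis "in which all randomised patients for whom outcome data are available, will be recorded".
- **Model** (same section): "repeated measures analysis of variance with adjustment for baseline characteristics".
- **Claim** (same section): "This analysis avoids the possibility of any bias associated with loss, misallocation or non-adherence of participants".

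**The concern.** Analysing patients in the arm to which they were randomised deals with misallocation and non-adherence. It does nothing for outcomes that were never measured. Here some of the loss depends on the outcome: a month-3 HbA1c above 8.5% ends participation, and so does a change of glucose-lowering agents, which is linked to HbA1c to the extent that poor control prompts it. The exit threshold is only 0.5 points above the entry ceiling (8.5 − 8.0).

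No section plans a month-6 HbA1c for a terminated patient. Repeated measures ANOVA in its classical form needs complete records, so such a patient would drop out together with the month-3 value that triggered the exit. If vitamin D works, this happens more often on placebo. The placebo arm then looks better than it was, and the difference shrinks. A reader who trusts the claim would take a diluted result as free of attrition bias. The additional per-protocol analysis cannot repair this, because it excludes more patients.

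**Working it through.** **1. Scale.** The plan gives no figure for this bias, but its sample size fixes the scale. Inputs from Sample size estimation: difference 0.5, SD 1.0, 5% significance (taken as two-sided), 80% power.

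n per arm = 2 × (1.960 + 0.842)² × 1.0² / 0.5² = 62.8, so 63 per arm and 126 in total, as stated. The effect at risk is therefore 0.50 HbA1c points.

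**2. Mechanism.** In each arm, with p the proportion who exit and g the gap in baseline-adjusted month-6 HbA1c between those who exit and those who stay:

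mean of those staying = mean of all − p × g

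observed difference = true difference − (p × g on placebo − p × g on active)

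The shift is zero when p and g are equal in both arms, as they are with no treatment effect. If the drug lowers HbA1c, p is larger on placebo and the observed difference is too small.

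**3. HbA1c above 8.5% at month 3 alone.** Simulation, true difference 0.50. Assumptions not in the document: baseline mean 6.7 to 7.0% after truncation at 8.0%, SD of change 0.5 to 1.0, correlation 0.7 between month-3 and month-6 change, half or all of the effect present by month 3.

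| SD of change | Month-6 SD, placebo | Exit, placebo | Exit, active | Completers' estimate |
|---|---|---|---|---|
| 0.5 to 0.7 | 0.76 to 1.03 | 0.9 to 4.8% | 0.1 to 2.4% | 0.47 to 0.49 |
| 1.0 | 1.15 to 1.26 | 6.7 to 10.0% | 2.6 to 6.7% | 0.43 to 0.47 |

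The second row implies a spread above the plan's own SD of 1.0, so it is an upper extreme. With no true effect, exit was 4.8% in both arms and the bias about zero.

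**4. Adding changes of agents.** Assumptions: HbA1c mean 7.0 to 7.2%, SD 0.8 to 1.0, correlation 0.7 between visits, entry cap 8.0%, agents changed in 30 to 60% of patients above 7.5% at month 3, half or all of the effect by month 3. Only month-3 values may trigger exit, because a value first seen at the final visit is itself the endpoint and causes no loss.

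- Exit: about 7 to 18% on placebo, 2 to 12% on active.
- Completers, baseline-adjusted: a true 0.50 is observed as 0.46 to 0.49. Attenuation runs from (0.50 − 0.49)/0.50 = 2% to (0.50 − 0.46)/0.50 = 8%.
- The same patients, unadjusted change from baseline: at most about 3% attenuation. The plan names baseline adjustment for the primary endpoint, so the adjusted range applies.

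I re-ran this step and obtained the same ranges.

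**5. What recovers the loss.** Predicting the missing month-6 value from arm, baseline and the month-3 value returned about 0.50 in every scenario. A likelihood-based model that keeps the month-3 value uses the same information.

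**6. What does not.** Pooling month-6 values measured after a change of agents, with an assumed 0.7-point fall from the change, gave 0.42 to 0.48. In each matched run that was further from 0.50 than the completers' estimate.

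**The case against.** The strongest reply is that several links are inferred.

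- **No month-6 value.** A reader might infer that terminated patients certainly have none. The text does not say so, and analysing patients whether or not they adhered suggests some measurement off treatment. What stands is that none is planned after termination.
- **The triggering value is lost.** A patient who exits at month 3 does have post-baseline outcome data, so a model could keep it. This stands as a possibility, but the named method does not do so in its classical form.
- **Change of agents as treatment failure.** The text gives neither direction nor reason for the change. The link to poor control is an assumption here.
- **Vitamin D criteria.** A reader might infer that exit at 25(OH)D below 15 nmol/l adds a one-sided loss on placebo. The same list contains 25(OH)D above 250 nmol/l and hypercalcaemia, which would fall mainly on active, and patients below 15 nmol/l are excluded at entry. No net direction can be claimed.
- **A larger bias.** Counting month-6 values as triggers gives removal of 16 to 28% on placebo and attenuation of 4 to 10%. That lets the endpoint cause its own absence, so those figures should not be used.

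Follow-up after withdrawal is also detail that an article may leave to the full protocol. That is fair for the missing detail, but not for the bias statement, which the article makes outright.

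**Conclusion.** The claim that the available-data ITT analysis avoids any bias from loss is wrong as written and should be corrected. Part of the loss depends on the primary outcome, and the stated analysis does not address it.

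The size is modest. Under the assumptions of step 4, a true 0.50 is observed as about 0.46 to 0.49. None of those inputs (mean, visit correlation, rate of agent changes, timing of effect) is in the document, and neither is any exit rate, so this is an illustrative range and not an estimate for this trial. The direction is towards no effect.

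A reader might infer that the trial could produce a false positive, or that its main result would be invalid. Neither follows: with no treatment effect the bias was about zero. This is a point to fix while recruitment is open, not one that undermines the design.

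**What to change.** 1. Delete the bias sentence, or limit it to misallocation and non-adherence and say that loss of outcome data can still bias the result.
2. Leave the clinical stopping criteria as they are. State that stopping study medication does not end follow-up, so that the scheduled month-3 and month-6 HbA1c are still collected.
3. Replace the repeated measures ANOVA with a likelihood-based mixed model by randomised arm that keeps every available HbA1c value, including a month-3 value that triggered stopping.
4. Record the date of any change of agents. State in advance whether the primary analysis uses HbA1c measured after it, and report the other choice as a sensitivity analysis.

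**Cost.** Amendment wording, a change of model, and one blood draw already on the schedule for patients off study medication.

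**Downside.** Item 4 is a real choice of what to estimate. Including HbA1c after a change of agents can dilute the difference by more than the loss it repairs (0.42 to 0.48 in step 6, against 0.46 to 0.49 in completers). Setting those values aside relies on the month-3 value predicting what is missing. It must therefore be settled before unblinding.
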